	**Exclusion criteria:**
	- Pre-capillary pulmonary hypertension
	- Congenital or acquired severe valvular diseases
	- Walking disability
	- Subject who participates in an interventional study during the course of this study
	- Severe lung disease
	- Active myocarditis, unstable angina pectoris, exercise-induced ventricular arrhythmias
	- Hemoglobin concentration less than 75% of the lower limit of normal
	- Systolic blood pressure < 85 mmHg
	- Pregnancy or lactation
	- History or suspicion of inability to cooperate adequately
Study type	Interventional, multicenter trial; intervention model description: randomized, controlled, parallel-group with crossover of the control group; masking: single (outcomes assessor); primary purpose: treatment
Date of first enrolment (estimated)	February 1, 2023
Target sample size	90
Recruitment status	Not yet recruiting
Primary outcome(s)	Changes in 6-min walking distance (time frame: baseline to 15 weeks)
Key secondary outcomes	Changes in peak exercise oxygen uptake, quality of life, echocardiographic parameters, natriuretic peptides (time frame: baseline to 15 weeks)

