### Assessments

#### Efficacy assessment

Efficacy parameters in both groups will be assessed at baseline and after 15 weeks (mean or median changes from baseline to 15 weeks, comparing changes within trained and control groups as well as mean/median changes between these groups). Patients in the training group will additionally perform the 6-MWD at the end of in-hospital rehabilitation.

The primary endpoint is to determine the effect of standardized exercise and respiratory training on exercise capacity, measured by the mean change of 6-MWD (baseline vs 15 weeks vs control group) in the HFpEF-PH population.

Secondary endpoints include mean/median changes from baseline to 15 weeks of echocardiography parameters, cardiopulmonary exercise testing, World Health Organization (WHO) functional class, measurement of safety parameters, health-related quality of life assessment (SF-36 questionnaire), anxiety and depression assessment (HADS scale), optional right heart catheterization at rest and during exercise, and optional cardiac magnetic resonance imaging (MRI). A detailed description of the evaluative parameters of each test is provided in the following paragraph (the “Procedures” section).

A follow-up interview will be performed by phone at the end of the study (last patient, last visit) to assess safety and compliance and observe survival. The long-term compliance and risk profile of exercise training will be explored to identify risk factors and record adverse events.

The detailed timeline of the study is shown in Fig. 1.

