#### Laboratory parameters

The N-terminal prohormone of brain natriuretic peptide (NTproBNP) will be assessed at baseline and after the 15-week follow-up period. Routine laboratory parameters determined according to the standards of the clinic (hemoglobin, glucose, creatinine, potassium, iron) will be collected as safety parameters.

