### Statistical considerations and analyses

#### Sample size calculation

To estimate the effect of exercise training on 6-MWD, 90 patients are expected to be enrolled, who either receive exercise training or continue their daily lifestyle for 15 weeks. The sample size was calculated by the G*Power 3.1 program according to the results of previous studies on 6-MWD. Based on previous data and the inclusion criteria, we expect a clinically significant mean increase of 35 m with a standard deviation of the difference of 50 m. If the true treatment effect is a difference of at least 35 m with an equal standard deviation of the difference of 50 m, the two-sided Student’s *t*-test at an alpha level of 0.05 has a power of 85%, if 38 patients for each group are included. To account for a possible 15% dropout rate, we will include 45 patients in each group—90 patients in total.

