#### Statistical analysis

The data from all centers will be pooled. If sample sizes allow, center effects on the primary and secondary outcomes will be analyzed.

Descriptive statistics will be displayed by treatment and control groups corrected for the active treatment group, including the usual location and scale statistics (mean, median, standard deviation, standard error, first and third quartiles, minimum, and maximum) and 95% confidence limits of the mean and median. Frequency tables for qualitative data will be provided. As an unbalanced distribution of baseline characteristics may not be completely excluded, baseline clinical parameters including patient risks and prognostic implications will be analyzed and compared between the groups.

The primary efficacy analysis will be based on an analysis of variance with the baseline values as a covariate (ANCOVA). This analysis provides a power advantage over the standard two-sided Student’s *t*-test leading to a statistical power of 85% or more. If the preconditions for ANCOVA are not met, a *t*-test with robust variance estimation (Welch test) will be used. Secondary endpoints will be analyzed by comparison of the mean changes between baseline and 15 weeks in the two groups (training vs control group) adjusted for the baseline value (ANCOVA or Wilcoxon rank sum test for non-parametric data). Categorical data will be analyzed by the McNemar test or chi-square test as appropriate. Exploratory data analysis of follow-up will be conducted by descriptive statistics and comparing baseline values and follow-up examinations. In case of ≤ 20% of missing values of a variable, a multiple imputation strategy will be used and analyzed as sensitivity analysis for data interpretation. The primary analysis set is the intention-to-treat analysis population (all patients randomized into the study). As a sensitivity analysis, the per-protocol population will be analyzed (all patients actually taking part in the study). Patients not fulfilling the inclusion criteria will be excluded in a separate sensitivity analysis using the per-protocol set.

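### NT-proBNP: every stated test works on absolute change, which costs power and gives no proportional effect, and two paragraphs disagree on the test (low severity)

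*Protocol article*

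**What the plan says.** **Status of the biomarker.** Table 1 of the protocol article gives as key secondary outcomes: "Changes in peak exercise oxygen uptake, quality of life, echocardiographic parameters, natriuretic peptides (time frame: baseline to 15 weeks". The abstract also lists prognostic biomarkers among the secondary endpoints. Under Laboratory parameters: "The N-terminal prohormone of brain natriuretic peptide (NTproBNP) will be assessed at baseline and after the 15-week follow-up period". The other laboratory values are collected for safety. The paragraph under Efficacy assessment begins "Secondary endpoints include mean/median changes from baseline to 15 weeks of echocardiography parameters, cardiopulmonary exercise testing" and does not name NT-proBNP.

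**Analysis.** The main paragraphs under Statistical analysis state: "Secondary endpoints will be analyzed by comparison of the mean changes between baseline and 15 weeks in the two groups". The same sentence goes on to promise adjustment for the baseline value, by ANCOVA or, where the data are non-parametric, by the Wilcoxon rank sum test. What makes data non-parametric is not defined.

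The closing paragraph of the section covers secondary and exploratory efficacy parameters. It assigns changes from baseline to week 15 to the Welch test, with no baseline adjustment and no rank alternative, and displays values as mean with SD or SEM. The descriptive statistics earlier in the section do include medians and quartiles.

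No analysis specific to NT-proBNP is given, and no transformation is named.

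**The concern.** Natriuretic peptides typically differ between patients by multiples, and their variation within a patient tends to grow with the level. On the absolute scale a fall from 6000 to 4500 is 1500 units and a fall from 600 to 450 is 150 units. The first counts ten times as much, although both are 25% reductions. On the log scale both equal ln(0.75) = -0.288.

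A mean comparison of absolute changes therefore gives most of its weight to patients with high values, and its residual spread grows with baseline. The rank sum alternative limits the pull of extreme values, but ranks of absolute change still depend partly on baseline level. That test makes no baseline adjustment, so it cannot do what its own sentence promises, and it yields no percentage change.

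At stake is the chance of detecting a real proportional effect on the one biomarker assessed outside the safety laboratory values, and the ability to report its size. Because the two paragraphs differ, three tests are available for this one endpoint.

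**Working it through.** **1. The plan's own figure.** The sample size concerns 6-MWD only: "we expect a clinically significant mean increase of 35 m with a standard deviation of the difference of 50 m", and "the two-sided Student’s *t*-test at an alpha level of 0.05 has a power of 85%, if 38 patients for each group are included". With the noncentral t, power is 84.4% at 37 and 85.3% at 38 per group. Dropout: 38 / (1 - 0.15) = 44.7, so 45. Both figures reproduce. The protocol gives no NT-proBNP distribution, effect or power, so every input below except 38 per arm and two-sided 0.05 is an assumption.

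**2. Log-scale ANCOVA, closed form.** If the log change has SD s and is unrelated to baseline, the standard error of the arm difference is s × √(2/38) = 0.2294 s.

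- s = 0.5: SE = 0.1147. A 30% reduction is |ln 0.70| = 0.357. The ratio is 0.357 / 0.1147 = 3.11. Power ≈ Φ(3.11 - 1.99) = Φ(1.12) ≈ 87%.
- s = 0.5, 25% reduction: 0.288 / 0.1147 = 2.51. Power ≈ Φ(0.52) ≈ 70%.

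Simulation of the first setting with log SD 1.0 gives 86% for log ANCOVA, 52% for raw ANCOVA and 72% for Wilcoxon on raw change.

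**3. Range over these assumptions.** With log SD 0.8-1.2, log-change SD 0.4-0.5 and reductions of 20-30%, the loss against log ANCOVA is about 16-44 power points for raw ANCOVA, 17-48 for Welch and 6-17 for Wilcoxon.

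**4. A second parametrisation.** Baseline and week-15 log values are given equal SD and correlation ρ of 0.8 or 0.9 (2000 runs per setting, 38 per arm). Power in %, with the loss against log ANCOVA in brackets, for the settings that fix the extremes and two central ones:

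| log SD | ρ | reduction | log ANCOVA | raw ANCOVA | Welch | Wilcoxon |
|---|---|---|---|---|---|---|
| 0.8 | 0.9 | 30% | 99.4 | 92.6 (6.8) | 80.4 (19.0) | 93.6 (5.8) |
| 1.0 | 0.8 | 30% | 71.2 | 44.0 (27.2) | 33.0 (38.2) | 49.4 (21.8) |
| 1.0 | 0.9 | 20% | 59.5 | 34.8 (24.7) | 27.4 (32.1) | 43.5 (16.0) |
| 1.0 | 0.9 | 30% | 93.6 | 68.4 (25.2) | 53.0 (40.6) | 79.0 (14.6) |
| 1.2 | 0.8 | 20% | 26.0 | 13.4 (12.6) | 11.0 (15.0) | 18.0 (8.0) |
| 1.2 | 0.9 | 30% | 83.3 | 48.2 (35.1) | 34.0 (49.3) | 62.4 (20.9) |

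The losses here run from about 7 to 35 points (raw ANCOVA), 15 to 49 (Welch) and 6 to 22 (Wilcoxon). The direction is the same in every setting.

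**5. Dominance by high values.** In these simulations the 4 most extreme of 76 patients carry about 56-73% of the sum of squares of the raw change. This affects the ANCOVA and Welch routes.

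**6. Which route skewed data would take.** A rule that moves from raw ANCOVA to Wilcoxon when residuals fail a Shapiro-Wilk test had power within about 0.3 points of Wilcoxon throughout. Under the main paragraphs, the Wilcoxon loss is therefore probably the relevant one. Under the closing paragraph it is the Welch loss.

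**7. Type I error.** With no true effect, rejection rates at 38 per arm were 3.4-5.5% across all four tests.

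**The case against.** The strongest reply is that the methods sentence already provides for skewed data. It offers the Wilcoxon test, the endpoint paragraph speaks of mean or median changes, and the descriptive statistics include medians and quartiles. This stands. A reader might infer that NT-proBNP must be analysed as a raw mean change and that a few very ill patients decide the result. The protocol does not support that: the rank alternative would probably be triggered, and it removes their dominance. A reader might also infer that such patients could create a false difference beyond ordinary chance. The simulated type I error does not support that either.

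Second, choosing a transformation for one laboratory variable is ordinary SAP content, and the SAP is not shown. This limits the severity but does not remove the point. The article does state tests for changes in secondary endpoints, and its two statements differ.

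Third, the size is assumed. A log-normal model with a constant ratio favours log ANCOVA by construction, and the trial promises no power for NT-proBNP. With a 10% reduction every method had only 8-20% power. The ranges illustrate the loss and do not predict this trial.

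Finally, a reader might take the absence of NT-proBNP under Efficacy assessment to mean that it is not a secondary endpoint. That list is worded as non-exhaustive, and Table 1 includes natriuretic peptides. It is a listing gap only.

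**Conclusion.** The point holds as a low-severity improvement to a secondary endpoint. On a plain reading, all stated routes for NT-proBNP use absolute change. The main paragraphs and the closing paragraph of Statistical analysis disagree on the test, and the rank alternative cannot deliver the baseline adjustment promised in its own sentence.

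Under the assumptions in step 3 of the working, log-scale ANCOVA gains about 6-17 power points over Wilcoxon, the likely route under the main paragraphs, and about 17-48 over Welch, the route in the closing paragraph. Against raw ANCOVA the gain is about 16-44. The second parametrisation moves the ends of these ranges but not the ordering. The cost of leaving the text as it is lies in power and interpretability. The 6-MWD analysis and its sample size are unaffected.

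**What to change.** 1. Analyse ln(week-15 NT-proBNP) by ANCOVA with ln(baseline) as covariate, and report the between-arm ratio of geometric means with 95% CI.
2. For this endpoint, replace the mean with SD or SEM display in the closing paragraph by geometric means, or by medians with quartiles.
3. Reconcile the main and closing paragraphs of Statistical analysis so that one primary test for NT-proBNP is named. If a rank test is kept, make it a sensitivity analysis and do not describe it as baseline-adjusted.
4. As a minor consistency edit, name NT-proBNP among the secondary endpoints under Efficacy assessment, to match Table 1.

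The cost is a few sentences in the protocol or SAP, settled before unblinding. No further patients, samples or visits are needed.

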Patient characteristics and efficacy parameters (secondary and exploratory endpoints) will be analyzed at baseline and 15 weeks. The values for each respective group will be displayed as mean ± standard deviation or mean ± standard error of the mean. Changes from baseline to 15 weeks will be analyzed by robust Student’s *t*-test (Welch test). Frequency data will be displayed as *n* and %. This data will be analyzed by the chi-square test and McNemar test. By means of correlation and regression analysis, the influence of different factors on the training effect will be investigated. *P*-values < 0.05 will be considered significant.

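### Studying factors that influence the training effect by correlation and regression, with no arm-by-factor interaction stated, can mistake prognosis or regression to the mean for a predictor of response

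*Protocol article*

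**What the plan says.** The last paragraph of the Statistical analysis section of the protocol article gives the method in one sentence: by correlation and regression, "the influence of different factors on the training effect will be investigated". The sentence after it sets the threshold: p-"values < 0.05 will be considered significant".

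The article does not list the factors, name the patients to be analysed, define the training effect for this purpose, or state an interaction term. The Sample size calculation section treats the effect as a contrast between groups: "If the true treatment effect is a difference of at least 35 m". The Efficacy assessment section also describes the primary endpoint with reference to the control group, but it plans comparisons of change within each group as well. The primary analysis is an ANCOVA with the baseline value as covariate. The sentence on factors is not tied to that model.

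**The concern.** A correlation needs one outcome value per patient. The difference between trained and untrained is not available per patient; change from baseline is. So the correlation part of the stated method can only relate a factor to change, and change mixes three things: the effect of training, the course the patient would have had anyway, and measurement noise. A factor that predicts the untreated course will correlate with change in trained patients even if training helps everyone equally. Baseline 6-MWD will correlate negatively with its own change for purely arithmetical reasons. A pooled regression with main effects only does not solve this, because the factor's coefficient is then its average association with outcome across both arms, which is prognosis.

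A reading based on trained patients alone is realistic. Within-group change is a planned comparison, and the Control section lets control patients train after week 15, with their final assessment reused as a training baseline.

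At stake is a statement about who benefits. The article presents this as the first exercise trial in this population, so a significant predictor of response could be read as guidance on selecting patients. The randomised control arm that would remove the artefact is already in the trial.

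**Working it through.** **Inputs from the article (Sample size calculation).** Difference 35 m; SD of the change 50 m; two-sided alpha 0.05; power 85%; 38 evaluable and 45 enrolled per group after 15% dropout.

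**Inputs assumed.** The correlation r between baseline and week-15 6-MWD, and equal SDs at the two times. The article gives neither.

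**1. The plan's own figure.** The article states that the t-test "at an alpha level of 0.05 has a power of 85"% "if 38 patients for each group are included". A two-sample t-test by the noncentral t gives power 0.853 at 38 per group and 0.844 at 37, so 38 is the smallest size that reaches 85%. For dropout, 38 / 0.85 = 44.7, rounded up to 45. The stated sample size reproduces.

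**2. Regression to the mean in one arm.** With equal SDs s and correlation r, SD(change) = s × √(2(1 − r)) and corr(baseline, change) = −√((1 − r)/2). A constant training effect shifts every change equally and leaves this correlation as it is.

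- r = 0.8: s = 50/√0.4 = 79.1 m; correlation −√0.1 = −0.316.
- r = 0.9: s = 50/√0.2 = 111.8 m; correlation −√0.05 = −0.224.

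The chance that this is significant at two-sided 0.05 follows approximately from Fisher's z, with λ = artanh(|ρ|) × √(n − 3) and probability Φ(λ − 1.96) + Φ(−λ − 1.96):

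| r | n trained | λ | Fisher z | Simulation |
|---|---|---|---|---|
| 0.8 | 38 | 1.94 | 49% | 50–51% |
| 0.8 | 45 | 2.12 | 56% | 57% |
| 0.9 | 38 | 1.35 | 27% | 27–28% |
| 0.9 | 45 | 1.47 | 31% | 32% |

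No effect modification is present in any row. A lower r makes it worse: at n = 38 the simulated rate is 68% for r = 0.7 and 90% for r = 0.5.

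**3. Prognosis.** Suppose a factor has the same correlation with change in both arms, with a constant 35 m effect and 38 per arm (4,000 simulated trials per row; the correlations are assumed).

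| Correlation with change, both arms | Significant in trained arm |
|---|---|
| 0.2 | 23% |
| 0.3 | 44% |
| 0.4 | 71% |
| 0.5 | 90% |

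**4. The interaction test on the same data.** Across all settings simulated with 38 per arm in steps 2 and 3, the arm-by-factor test rejected in 4.4–5.4% of trials, which is its nominal level.

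**5. What the interaction test can detect.** For a 50/50 binary factor and N patients in four equal cells, SE = 50 × √(4/(N/4)).

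- N = 76: SE = 50 × √(4/19) = 22.9 m; 35/22.9 = 1.53; power 33%; 80% power needs (1.96 + 0.84) × 22.9 ≈ 64 m.
- N = 90: SE = 50 × √(4/22.5) = 21.1 m; 35/21.1 = 1.66; power 38%; 80% power needs about 59 m.

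These use the SD of change. Under the assumptions of step 2, baseline adjustment lowers the residual SD only to 50 × √((1 + r)/2), which is 47.4 m at r = 0.8 and 48.7 m at r = 0.9, so the picture hardly changes.

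**The case against.** The strongest reply is that the defect is read out of silence. The sentence does not confine the analysis to trained patients and does not exclude interactions, and regression can contain them. The article elsewhere describes the effect against control and adjusts for baseline in its ANCOVA. A condensed article commonly leaves the form of an exploratory model to the full protocol or analysis plan, which are not shown.

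Much of this stands. A reader might infer that the plan rules out interactions, or that it will report false predictors. The text supports neither: interactions are unstated, and the error depends on the model and patients chosen. A reader might also take 27–57% as the error rate for all factors. It applies to baseline 6-MWD correlated, unadjusted, with its own change in the trained arm under assumed values; coupling affects mainly that variable and its correlates. Nor does the point extend to the long-term follow-up in the Efficacy assessment section, which is meant "to identify risk factors and record adverse events". That concerns safety and compliance, not modification of the 15-week effect.

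What the objection does not answer is the correlation half of the stated method. A bivariate correlation has no place for an interaction term, so it cannot address its stated aim whatever a fuller plan adds about the regression.

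**Conclusion.** The concern holds in limited form. The article names a method, and a significance threshold, that cannot by correlation alone separate effect modification from prognosis or regression to the mean, and it states no interaction that would.

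If the analysis is run on individual change in trained patients, false significance is about 27–57% for baseline 6-MWD at r of 0.8 to 0.9 with equal SDs and 38 to 45 patients. It is 23–90% for purely prognostic factors with an assumed correlation of 0.2 to 0.5 with change and 38 trained patients. The interaction test stays near 5%. All these ranges rest on values that the article does not give.

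The primary ANCOVA, the sample size and the main conclusion are untouched. This is a minor point on an exploratory analysis.

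**What to change.** Replace the sentence with wording that does three things:

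- **Define the target.** The training effect is the between-arm difference in the week-15 outcome.
- **Test baseline factors by interaction.** For each one, add the factor and an arm-by-factor term to the baseline-adjusted ANCOVA (week-15 value on arm, baseline value, factor, arm × factor) in all randomised patients. Where the factor is the baseline value itself, add only its interaction with arm. Report the interaction estimate with its 95% CI, labelled exploratory.
- **Keep trained-only factors separate.** Training intensity and duration from the patient diary exist only in the training arm, so no interaction can be estimated for them. They may be described within that arm, adjusted for the baseline value, as descriptive associations and not as predictors of the training effect.

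The cost is a change of analysis wording; no extra patients or data are needed. The downside is imprecision: with a 50/50 binary factor, power is only about 33–38% for an interaction as large as the 35 m planned effect. A non-significant interaction would therefore not show that the effect is uniform, and the report should say so.

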**Methods:**

A total of 90 stable patients with HFpEF-PH (World Health Organization functional class II–IV) will be randomized (1:1) to receive a 15-week specialized low-intensity rehabilitation program, including exercise and respiratory therapy and mental gait training, with an in-hospital start, or standard care alone. The primary endpoint of the study is a change in 6-min walk test distance; secondary endpoints are changes in peak exercise oxygen uptake, QoL, echocardiographic parameters, prognostic biomarkers, and safety parameters.

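### The plan labels every secondary and exploratory p-value below 0.05 significant, without adjustment, across roughly 37 to 51 variables, so at least one chance finding is likely; the primary 6-MWD conclusion is not affected

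*Protocol article*

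**What the plan says.** The Abstract names a single primary endpoint: "The primary endpoint of the study is a change in 6-min walk test distance".

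The secondary endpoints are whole test batteries. The Efficacy assessment section states: "Secondary endpoints include mean/median changes from baseline to 15 weeks of echocardiography parameters, cardiopulmonary exercise testing, World Health Organization (WHO) functional class", and goes on to safety parameters, SF-36, HADS, and optional catheterisation and MRI. It then defers to the Procedures section for the variables: "A detailed description of the evaluative parameters of each test is provided in the following paragraph".

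Table 1 has a shorter list of key secondary outcomes: "Changes in peak exercise oxygen uptake, quality of life, echocardiographic parameters, natriuretic peptides (time frame: baseline to 15 weeks").

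The Statistical analysis section makes these endpoints subject to formal between-group tests: "Secondary endpoints will be analyzed by comparison of the mean changes between baseline and 15 weeks in the two groups", by ANCOVA or Wilcoxon rank sum test. Its last paragraph opens with "Patient characteristics and efficacy parameters (secondary and exploratory endpoints) will be analyzed at baseline and 15 weeks", adds Welch, chi-square and McNemar tests and regression analyses, and closes with the rule that p-"values < 0.05 will be considered significant". Nothing in the article limits that rule for any secondary or exploratory endpoint.

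**The concern.** A threshold of 0.05 limits the error of one test. Applied separately to dozens of tests, it does not limit the chance that some of them cross it by accident.

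This matters because the Abstract and Background set out to learn whether training may improve quality of life, haemodynamics, diastolic function and biomarkers as well as exercise capacity. Apart from the walk distance itself, all of these rest on secondary endpoints. Under the rule as written, a single SF-36 subscale or strain value at p = 0.04 could be reported as a significant improvement, in a 90-patient trial that presents itself as the first in this population. Readers would have no stated basis for telling such a result from one that was prioritised in advance.

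**Working it through.** **The plan's own figure.** The article gives no familywise error rate, so the only figure to reproduce is the sample size. With a difference of 35 m and SD 50 m, d = 35/50 = 0.7. The noncentral t distribution (two-sided alpha 0.05) gives power 0.844 at 37 per group and 0.853 at 38, so 38 is the smallest number for 85%. Allowing for dropout, 38/0.85 = 44.7, rounded up to 45. The primary test is one test at 0.05, with a 2.5% chance of a false result favouring training.

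**Number of secondary variables.** The article gives no total. I counted from Procedures, plus WHO functional class from the Efficacy assessment section:

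- Cardiopulmonary exercise test, 10: peak VO2 absolute and per kg, workload, ventilation, VE/VCO2, heart rate, saturation, blood pressure, and VO2 and VCO2 at the anaerobic threshold.
- Echocardiography, 13: chamber sizes (counted once), LV ejection fraction by two methods, E/e′, RV FAC, 3D RV ejection fraction, sPAP, TAPSE, TAPSV, RV strain, LV strain, and vena cava size and collapsibility.
- SF-36, 10 (two main scores, eight subscales).
- HADS, 2.
- WHO functional class, 1.
- NT-proBNP, 1.

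Sum: 10 + 13 + 10 + 2 + 1 + 1 = 37. Optional resting catheterisation adds 6 and optional MRI about 8: 37 + 6 + 8 = 51.

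The count is approximate. It leaves out separate chambers, exercise haemodynamics, the Borg score, within-group comparisons, and any second p-value from running both ANCOVA and a Welch test on the same endpoint.

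**Independent tests, no true effect.**

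- At least one p < 0.05 in either direction: 1 − 0.95^37 = 0.850; 1 − 0.95^51 = 0.927.
- At least one favouring training (0.025 per test): 1 − 0.975^37 = 0.608; 1 − 0.975^51 = 0.725.
- Expected number in either direction, whatever the correlation: 37 × 0.05 = 1.85; 51 × 0.05 = 2.55. Half of these favour training: about 0.93 and 1.28.

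**Correlated tests.** The article gives no correlations, so these are assumptions. I simulated 200,000 sets of standard normal test statistics, scored so that positive values favour training. The model was z = √ρ·g + √(1−ρ)·e, with g shared by all tests and e specific to each. One variant had correlation 0.5 within a test battery and 0.2 between batteries. I counted sets with any |z| > 1.96, and sets with any z > 1.96.

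| Assumed correlation | Either direction, 37 tests | Either direction, 51 tests | Favouring training, 37 tests | Favouring training, 51 tests |
|---|---|---|---|---|
| 0 (formula) | 85% | 93% | 61% | 73% |
| 0.3 throughout | 72% | 81% | 39% | 45% |
| 0.5 within, 0.2 between | 69% | 80% | 38% | 46% |
| 0.5 throughout | 55% | 63% | 28% | 32% |
| 0.7 throughout | 36% | 41% | 18% | 20% |

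**Table 1 list only.** One peak VO2, 10 SF-36 scores, 13 echocardiographic variables and one natriuretic peptide make 25. If independent, 1 − 0.95^25 = 0.72 in either direction and 1 − 0.975^25 = 0.47 favouring training.

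**The case against.** **The confirmatory claim is protected.** There is one primary endpoint, sized and tested once at 0.05. This stands in full: the point does not touch the 6-MWD conclusion.

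**The full protocol or SAP may handle multiplicity.** Neither is shown, and silence on a method would be no fault in a condensed article. But the article is not silent. It fixes a significance label for a paragraph that expressly covers secondary and exploratory endpoints, and the point rests on that stated rule alone.

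**A reader might take 85–93% as the chance of a false benefit.** The figures do not support that. They count results in both directions, and a benefit is only the favourable tail. At correlations of 0.3–0.5 throughout, a false favourable result is less likely than not. Independence is doubtful, because many measures overlap: VO2 with VO2/kg, two methods for LV ejection fraction, SF-36 component scores with their subscales. For some variables, such as heart rate and blood pressure during exercise testing, the article states no direction of benefit.

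**A reader might also infer that one significant secondary variable is meant to establish efficacy.** The article does not say so; it asks only whether training may improve these outcomes. What it permits is the label, and the label is what invites the claim.

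**The count is mine, and 51 includes optional tests.** This stands, and the totals should be read as orders of magnitude. Table 1 does show some priority, but it gives its four domains no separate testing status, and two of them are families of variables.

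**Conclusion.** The point holds as a fault in a stated decision rule. If there is no true effect, at least one secondary result in either direction would be called significant with probability 85–93% under independence and about 55–81% at correlations of 0.3–0.5. For a result favouring training, the figures are 61–73% and about 28–45%; even the lowest of these is about eleven times the 2.5% of the primary test (28/2.5 = 11.2).

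These sizes depend on an approximate count of 37 to 51 variables, on correlations the article does not give, and on no effect on any secondary variable. At a correlation of 0.7 throughout they fall to 36–41% in either direction and 18–20% favouring training. The direction of the conclusion does not depend on the exact count. It is worth correcting before analysis, but it is a matter of what the secondary results may be said to show. It does not threaten the trial's main result.

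**What to change.** Replace the closing sentence of the Statistical analysis section with a rule that reserves the word significant for the primary 6-MWD test. State that secondary and exploratory endpoints are reported as estimated differences with 95% confidence intervals and nominal p-values, and that these support no efficacy claim on their own.

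If the sponsor wants confirmatory secondary claims, name in advance one variable for each of the four Table 1 domains and test them only if the primary test succeeds. With Holm adjustment the ordered p-values are compared with 0.05/4 = 0.0125, 0.05/3 = 0.0167, 0.05/2 = 0.025 and 0.05, stopping at the first failure. Peak VO2, the SF-36 physical component score, E/e′ and NT-proBNP are one possible set. The choice is the sponsor's, and the wording change alone would settle the point.

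The cost is that fewer secondary results can be called significant. Data collection, sample size and primary power do not change.
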